**Fig. 2 Fig2:**
[figure not shown]
Sham acupuncture used in this trial

### Outcome measures

#### Primary outcome measures

The primary outcome of this study is the change in the NIH-CPSI total score, which will be measured from baseline to the 8^th^ week. After we have collected data for 8 weeks, the average score from each week will be calculated.

The NIH-CPSI is a validated, self-reported questionnaire that is widely used to assess CP/CPPS patients [24, 25]. It contains 13 items that are scored in three discrete domains: pain, urinary symptoms and impact on quality of life. A score of 0 indicates that the condition described in the question never occurs.

The secondary outcome measures include the following (for the first three secondary outcomes, we will measure the change from baseline):NIH-CPSI total score at the 20^th^ and 32^nd^ week.NIH-CPSI subscale scores at the 4^th^, 8^th^, 20^th^, and 32^nd^ week.IPSS total score at the 4^th^, 8^th^, 20^th^, and 32^nd^ week. The International Prostate Symptom Score (IPSS) is another valid, reliable and sensitive measure for patients with lower urinary tract symptoms (LUTS). The IPSS has been translated into several languages, including Chinese, and it is widely used in clinical practice and research to determine the severity of LUTS, including incomplete bladder emptying, frequency of urination, intermittency, urgency, weak urine stream, straining and nocturia [26, 27]. Each of the questions is rated from 0 (not at all) to 5 (almost always), and according to the total symptom score, the severity of LUTS can be graded as mild (0–7), moderate (8–19) or severe (20–35).Global response assessment at the 4^th^, 8^th^, 20^th^, and 32^nd^ week. Patients who have at least a 50 % decrease compared to baseline in total NIH-CPSI score will be considered “responders”. We will compare the response rate between the two groups.Expectations that acupuncture might help CP/CPPS at baseline. This scale includes four brief questions to investigate whether patients are confident that acupuncture treatment will help their CP/CPPS.The degree of satisfaction for patients undergoing acupuncture treatment will be measured at the 8^th^, 20^th^, and 32^nd^ week.

Table 1 shows the time to visit and the data collection measurements at different time points.

### Safety assessment

Adverse events (AEs) related to acupuncture treatment will be appropriately assessed and recorded by the observers throughout the trial, for instance, pain, haematomas, or nausea. AEs will be managed by acupuncturists and related clinical specialists within 24 h. The principal investigator ([name]) will make the final decision to terminate the trial if severe AEs arise.

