### Design

This study is a multi-centre, sham-controlled, randomized trial of acupuncture for the treatment of CP/CPPS that will be conducted in the Guang’anmen Hospital of China Academy of Chinese Medical Sciences and Yantai Hospital of Traditional Chinese Medicine from November 2015 to May 2017. All of the patients will be asked to sign an informed consent form prior to randomization. Blinded evaluators and statisticians will manage all data. We developed this protocol according to the Standard Protocol Items: Recommendations for Interventional Trials (SPIRIT) checklist [16]. This trial protocol has been approved by the Research Ethical Committee of Guang’anmen Hospital of China Academy of Chinese Medical Sciences and Yantai Hospital of Traditional Chinese Medicine, and it has been registered under the identifier NCT02588274 at ClinicalTrials.gov in the USA. Figure 1 provides a study flow chart.

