In this trial, we aim to clarify the efficacy and safety of acupuncture for treating CP/CPPS. We will calculate the mean NIH-CPSI scores over 8 weeks, and these scores will indicate the weekly efficacy of acupuncture during the 8 weeks of treatment; additionally, the mean value may provide more sufficient evidence for determining whether acupuncture is efficacious for treating CPPS. Furthermore, we will add an expectations scale to explore whether the patients’ expectations have a potential impact on the outcomes of acupuncture treatment. Nevertheless, this study has several limitations, including the small sample size and the unblinded acupuncturists. Due to the use of a sham acupuncture control, a relatively high rate of dropouts might be observed in the control group. Additionally, there is a risk that the blinding method may be unsuccessful in control participants, as the blunt tip needle will not leave puncture holes. Finally, a few participants might be recruited mistakenly due to the overlapping symptoms of CP/CPPS and BPH [41]. Nonetheless, the outcome assessors and patients will be blinded to decrease the potential for bias [42]. We hope that the results of this trial can provide both an evidence-based treatment option for patients suffering from CP/CPPS and an enhanced level of evidence on which to base guideline recommendations.

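### The article's only adverse event rule makes relatedness to acupuncture a condition of recording, so events judged unrelated are lost and recorded rates by arm depend on a prior causality judgement

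*Protocol article*

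**What the plan says.** The Safety assessment section holds the whole of the article's rule on collecting adverse events: "Adverse events (AEs) related to acupuncture treatment will be appropriately assessed and recorded by the observers throughout the trial". The examples given are "for instance, pain, haematomas, or nausea". Handling is assigned separately: "AEs will be managed by acupuncturists and related clinical specialists within 24 h". No causality criteria are given, and no other section provides for recording events whatever their cause.

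Three other places bear on the point.

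- **Aim.** The Discussion says "we aim to clarify the efficacy and safety of acupuncture for treating CP/CPPS".
- **Who can know the arm.** The Discussion concedes that "this study has several limitations, including the small sample size and the unblinded acupuncturists". It also sees a threat to blinding in the control arm, "as the blunt tip needle will not leave puncture holes".
- **Blinding claims.** The Design section says "Blinded evaluators and statisticians will manage all data", and the Discussion says "the outcome assessors and patients will be blinded to decrease the potential for bias". Neither statement names the observers who record adverse events or whoever judges relatedness.

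**The concern.** In a sham-controlled trial, safety data by arm are informative only if events are ascertained in the same way in both arms. Here a judgement of cause comes before the event enters the record, which has two consequences.

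1. **Loss of events.** Anything judged unrelated, such as an infection that nobody links to needling, is not recorded as an adverse event in either arm. If the judgement was wrong, or if a pattern shows only when events are pooled, the adverse event data hold nothing to re-examine.
2. **Attribution mixed with incidence.** Of the three examples, pain and nausea are not specific to needling. Pain is also a defining symptom of the condition and a domain of the NIH-CPSI. Whether new or worse pain was caused by treatment is therefore a real judgement. It may come out differently where needles go 25–60 mm deep than where a blunt tip does not penetrate the skin.

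At stake is the safety statement that the Discussion promises, not the primary efficacy result.

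**Working it through.** The article states no adverse event rate or causality share, so there is no figure to reproduce. The first part of the check is a reading of the text; the second is an illustration on assumed values.

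**1. Reading the text**

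- *Scope.* In the Safety assessment sentence, relatedness qualifies what is assessed and recorded. It is not a field completed after recording.
- *Who does what.* Observers assess and record; acupuncturists and clinical specialists manage. The acupuncturists are unblinded. The observers' blinding is not stated.
- *What is caught elsewhere.* Table 1 schedules the NIH-CPSI total at weeks 1 to 8, 20 and 32, and the NIH-CPSI subscales and IPSS at weeks 4, 8, 20 and 32, with no relatedness filter. Worsening urinary symptoms are therefore captured in both arms. The Control group section has all medication use recorded and compared between groups, so a treated infection may leave a trace there. Neither source is an adverse event record.
- *Contacts.* There are 24 sessions, three a week for 8 weeks. After that Table 1 shows contacts only at weeks 20 and 32.

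**2. Illustration**

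From the article: 34 patients per group, two-sided 5% level. Assumed: a true event rate t equal in both arms, and the shares of events judged related, q_A (acupuncture) and q_S (sham). The recorded rate in an arm is t × q, and the expected number of recorded patients is 34 × t × q.

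At t = 20%:

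- 90% v 50%: 0.20 × 0.90 = 18% and 0.20 × 0.50 = 10%, about 6.1 v 3.4 patients. An apparent 8-point difference where none exists.
- 80% v 60%: 0.20 × 0.80 = 16% and 0.20 × 0.60 = 12%, about 5.4 v 4.1 patients. An apparent 4-point difference.
- Equal shares of 50%: 10% v 10%. No false difference, but half the events are missing.

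The probability of a false significant difference, by an exact two-sided Fisher test at 5% with 34 per arm, is:

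| True rate, both arms | All events recorded | 80% v 60% | 70% v 40% | 90% v 50% | 90% v 30% |
|---|---|---|---|---|---|
| 10% | 1.2% | 0.9% | 0.8% | 1.8% | 3.3% |
| 20% | 2.4% | 3.3% | 4.8% | 8.2% | 18.8% |
| 30% | 2.7% | 5.2% | 9.8% | 15.0% | 37.9% |

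With moderate attribution gaps or low event rates, false significance stays rare in a trial this small. The recorded percentages are still distorted, and the large figures need an extreme gap. In all the unequal cases shown the error overstates harm from acupuncture; it does not hide it. The loss of events judged unrelated works the other way, by understating event rates in both arms.

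**The case against.** The strongest reply is that the article condenses a fuller protocol. It never says that unrelated events will not be recorded, and the sentences that follow in the same section speak of adverse events without the qualifier. Causality forms and case report form content usually sit in the full document. Part of this stands: the restriction is inferred from the sentence being the sole collection rule. But the sentence states a scope; it is not silent on the matter. If the full protocol collects all events, the published sentence misdescribes it and needs correcting anyway.

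Three stronger readings are tempting, and the article does not support them.

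- *That the recording is done unblinded.* The acupuncturists are given management, not recording. Blinded evaluators and outcome assessors are claimed, although not tied to the adverse event observers. Differential attribution is therefore possible but not shown. Blinding the observers would reduce it, but would not restore events judged unrelated.
- *That worsening urinary symptoms go uncaptured, or that every filtered event leaves no trace.* The NIH-CPSI and IPSS measure urinary symptoms in both arms, and the medication record may reveal some other events.
- *That a planned between-arm safety test is biased.* None is planned. The Aim section names efficacy alone, and neither the outcome list nor Table 2 contains a safety outcome. Comparison by arm is inferred from the Discussion's safety aim and the sham-controlled design.

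**Conclusion.** The point holds in a limited form. The only adverse event rule in the article makes relatedness the condition for recording, and this is a poor choice for a sham-controlled trial that says it will clarify safety. Events judged unrelated would not be recorded as adverse events in either arm, and recorded rates of non-specific complaints would depend partly on who is thought to have been needled.

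The size is unknown. With a true rate of 20% in both arms, the assumed shares of 80% v 60% and 90% v 50% give false differences of 4 and 8 percentage points. These rest entirely on assumed attribution shares and an assumed event rate, and if attribution is equal the false difference is zero. The loss of events judged unrelated does not depend on unequal attribution or on unblinded observers. The change is worth making, though the efficacy analysis does not depend on it.

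**What to change.** Reword the Safety assessment section so that:

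1. all adverse events are recorded in both arms regardless of presumed cause, at the treatment-phase visits and at the week 20 and week 32 follow-ups;
2. relatedness is classified after recording, as a separate field, where possible by someone blinded to arm;
3. all-cause and related events are both reported descriptively by assigned group, with no need for a formal test at this sample size.

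The article should also state whether the observers who record adverse events are blinded. If the full protocol already collects all events, correcting the sentence is enough.

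Cost: a case report form change and slightly more data entry, at contacts that are already scheduled. Because there is no scheduled contact between week 8 and week 20, or between weeks 20 and 32, follow-up events would rest on recall over 12 weeks. The report should say so. Nothing in the treatment or clinical management of patients changes.

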### Data collection and quality control

Because nonstandard input of clinical data can contribute to the bias of results, two investigators (to assess the effect of treatment) will independently collect the data using case report forms and then input the data into a computer; this process will ensure the safety and reliability of the data. To confirm the quality of the trial, all acupuncturists will be required to have an official license and more than two years of clinical experience.

### Sample size calculation and statistical analysis

The calculation of sample size was based on the primary outcome of change in NIH-CPSI total score from baseline to the 8^th^ week of treatment (mean of 8 weeks of data). According to previous literature [12], after 10 weeks of sham acupuncture treatment, NIH-CPSI scores decreased by 6.2, with a standard deviation of 10.3. We estimated that for a 13.3-point difference in the NIH-CPSI score with a standard deviation of 4.5, and based on our clinical experience and data from previous research, the decrease in the NIH-CPSI total score should be more than 6 points (i.e., the minimal clinically important difference, MCID) [28]. Therefore, we will need to recruit 34 patients per group from Guang’anmen Hospital of Chinese Academy of Chinese Medical Sciences and Yantai Hospital of Traditional Chinese Medicine to obtain 90 % power and a significance level of 5 % while allowing for a 20 % dropout rate.

The data will be analysed using SPSS software Ver.19.0 (IBM SPSS Statistics, IBM Corp, Somers, New York), and the data analysis will be based on the intention-to-treat (ITT) principle regarding baseline characteristics. If there are significantly more dropouts in the control group than in the treatment group, we will conduct a secondary analysis of subjects who have completed the treatment according to the protocol. The outcomes for evaluating changes between the groups will be based on the outcome of the NIH-CPSI at different time points. The significance levels will be two-sided and reported at a 5 % level. For continuous measurement data, the mean, standard deviation, median and interquartile range will be represented. If the data are normally distributed, analysis of covariance will be used because the centres and baseline variables in this study are covariates that are not manipulated by the researchers but may still have an effect on the efficacy of acupuncture. If the distribution is not normal, we will use generalized estimating equations, if needed, to account for the cumulative acupuncture frequency and to observe whether increasing treatment sessions results in increased efficacy for patients. Linear regression will be used to explore whether the patients’ expectations have an impact on treatment. For categorical data, a CMH (Cochran-Mantel-Haenszel) test will be used, and the data will be represented as case and percentages. Missing data will be assumed to be missing randomly and will be imputed using multiple imputation.

Table 2 summarizes the details of the analysis methods for the primary and secondary outcomes.

**Table 2 Tab2:** Analysis methods for outcomes

Outcomes	Time frame	Statistics
Primary outcome		
NIH-CPSI total score and change from baseline	baseline, week 1-8	Covariance analysis or generalized estimating equations
Secondary outcomes		
NIH-CPSI subscales score	Baseline, week 4,8,20,32	Covariance analysis or generalized estimating equations
NIH-CPSI total score in follow-up	week 20,32	Covariance analysis or generalized estimating equations
IPSS total score and change from baseline	baseline, week 4,8,20,32	Covariance analysis or generalized estimating equations
Global response assessment improvement	week 4,8,20,32	CMH test or nonparametric test
Degree of expectation	baseline	linear regress
Degree of satisfaction	week 8,20,32	CMH test or nonparametric test

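### The sample size paragraph gives 13.3 points (SD 4.5) as the difference, but 34 per group corresponds to a between-group difference of 7.1 points; N is right, the stated design difference is wrong

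*Protocol article*

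**What the plan says.** All the planning figures stand in one paragraph of the protocol article, under *Sample size calculation and statistical analysis*.

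- Sham arm, from a cited trial: "after 10 weeks of sham acupuncture treatment, NIH-CPSI scores decreased by 6.2, with a standard deviation of 10.3".
- Planning effect: "We estimated that for a 13.3-point difference in the NIH-CPSI score with a standard deviation of 4.5".
- Clinical threshold: "the decrease in the NIH-CPSI total score should be more than 6 points (i.e., the minimal clinically important difference, MCID".
- Conclusion: "we will need to recruit 34 patients per group", "to obtain 90 % power and a significance level of 5" per cent, "while allowing for a 20 % dropout rate".

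The analysis text that follows in the same section fixes the sidedness: "The significance levels will be two-sided and reported at a 5 % level". Allocation is 1:1 (*Recruitment procedures*), and the total is 68 (*Abstract*, *Participants*).

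The paragraph does not say that 13.3 is the expected change in the acupuncture arm. It states no between-group difference of 7.1 and does not say which SD or SDs entered the calculation.

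**The concern.** In a two-arm sample size paragraph, a difference with an SD attached is normally taken as the between-group effect for which the trial is powered. Read that way, 13.3 points with SD 4.5 is a very large standardised effect (13.3/4.5 = 2.96) and needs only a handful of patients. It does not lead to 34 per group, although the text presents 34 as its consequence.

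Two things are at stake.

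- **The planning effect.** Someone reading the results will judge a null or borderline finding against the effect the trial was sized for. If that is thought to be 13.3 points, a true effect of 7 points looks like a failure, when it is almost exactly what was planned.
- **The variance assumption.** The calculation uses an acupuncture-arm SD of 4.5 beside a sham-arm SD of 10.3, a ratio of 0.44. The 90% power depends on this inequality, and the present wording hides it.

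**Working it through.** **Inputs**, all from *Sample size calculation and statistical analysis* unless noted: two-sided alpha 0.05 (z = 1.96); power 90% (z = 1.2816); sham decrease 6.2, SD 10.3; the stated 13.3, SD 4.5; MCID 6; dropout 20%; allocation 1:1 (*Recruitment procedures*).

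**Formula**, normal approximation: n per group = (1.96 + 1.2816)² × (s1² + s2²) / d², rounded up. Recruited per group = n / 0.8, rounded up. The first factor is about 10.51.

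**Step 1. Reproduce 34.** Take 13.3 (SD 4.5) and 6.2 (SD 10.3) as the two arm decreases.

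- d = 13.3 − 6.2 = 7.1, so d² = 50.41.
- s1² + s2² = 106.09 + 20.25 = 126.34, equivalent to a common SD of √(126.34/2) = 7.948.
- n = 10.51 × 126.34 / 50.41 = 26.33, so 27.
- 27 / 0.8 = 33.75, so 34.

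This matches the stated figure and uses every number given for the two arms. A t-based calculation gives 28 evaluable and 35 recruited, one more per group.

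**Step 2. Take 13.3 as the between-group difference** (d² = 176.89).

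| SDs (two arms) | n evaluable | n recruited |
|---|---|---|
| 4.5 / 4.5 | 2.41 → 3 | 4 |
| 10.3 / 4.5 | 8 | 10 |
| 10.3 / 10.3 | 13 | 17 |

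One-sided tests and t-based versions do not exceed 18 recruited per group. The last row gives 34 in total, but the protocol says 34 per group and 68 overall.

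**Step 3. Take 6 points as the between-group difference** (d² = 36).

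| SDs (two arms) | n evaluable | n recruited |
|---|---|---|
| 4.5 / 4.5 | 12 | 15 |
| 10.3 / 4.5 | 36.9 → 37 | 47 |
| 10.3 / 10.3 | 62 | 78 |

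None of these gives 34.

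**Step 4. A near match.** 13.3 − 6 = 7.3 with SDs 10.3 and 4.5 gives 32 to 34 recruited, depending on the test. It subtracts the MCID from an arm's change, and nothing in the text supports that.

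**Step 5. Power at the stated N**, unadjusted, SDs 10.3 and 4.5. Power (normal) = Φ(d / √(126.34/n) − 1.96).

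| Difference | n per group | Normal | Welch t |
|---|---|---|---|
| 7.1 | 27 | 90.7% | 89.1% |
| 6 | 27 | 79.2% | 77.0% |
| 6 | 34 | 87.6% | 86.1% |

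For example, at 6 points with n = 27: √(126.34/27) = 2.163; 6/2.163 − 1.96 = 0.81; Φ = 0.792.

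**The case against.** The best defence is that no calculation is wrong. The stated 34 follows exactly from the paragraph's own figures, and the text never calls 13.3 a between-group effect. The paragraph opens with change from baseline, gives the sham decrease, then 13.3 with its own SD, so the word could mean a before-after difference in the second arm. This stands in part: N is right, and the intended meaning can be recovered. But the reader has to recover it by trial and error. The word printed is the one normally used for the treatment effect, and the real design difference is missing. An unseen analysis plan would not cure a quantity that is misnamed here.

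Three stronger readings are tempting, and the document does not support them.

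- **That the plan contradicts itself by lacking 90% power at the MCID.** It never promises 90% power at exactly 6 points. A design difference of 7.1 lies above that threshold, and choosing one above the MCID is ordinary practice. Lower power at 6 points is a limitation to disclose. The unadjusted figures also leave out the planned analysis of covariance. With a common SD of 7.948, 90% at 6 points would need a covariate correlation with the change score of about 0.52 with 27 per group, or 0.28 with 34. The protocol gives no correlation, so this gain is possible but not established.
- **That a sham decrease of 6.2 makes a 6-point MCID unusable.** A within-arm change does not invalidate a between-group threshold.
- **That the true power is about 70% at 7.1 points, or 56% at 6 points.** These figures (Welch t, 27 completers) need an SD of 10.3 in both arms, which the protocol did not adopt. They are a sensitivity scenario only.

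**Conclusion.** The point holds as an error in the stated design difference, not in the sample size. The paragraph attaches 13.3 points to the word difference, whereas 34 per group corresponds to 7.1 points; 13.3/7.1 = 1.87. As a between-group effect, 13.3 would need 4 to 17 recruited per group, at most half of what is planned.

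The conclusion assumes a two-sided 5% test, 90% power, equal allocation, inflation by 1/(1 − 0.2), and the normal approximation with the two arm SDs. The identification of 7.1 is an inference, since the protocol does not print it. It is nevertheless the only reading supported by the text that gives 34 per group.

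The 90% claim belongs to 7.1 points with SDs 10.3 and 4.5. At a 6-point between-group difference, unadjusted and with the same SDs, power is about 77–79% with 27 completers per group and 86–88% with all 34, before any gain from covariate adjustment. A reader might infer that the trial is too small or that N was miscalculated. Neither follows.

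**What to change.** Rewrite the paragraph so that it states:

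- an expected decrease of 13.3 (SD 4.5) with acupuncture and 6.2 (SD 10.3) with sham;
- a between-group design difference of 7.1 points;
- 27 evaluable per group, 34 per group after allowing for 20% dropout, 68 in total;
- that the 90% power applies at 7.1 points and not at the 6-point MCID.

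The authors should first confirm from their planning records that these were the inputs. If they also quote power at a 6-point between-group difference, they should give the assumptions with it: unadjusted test, SDs 10.3 and 4.5, and the number of completers. Any result with SD 10.3 in both arms should be labelled a sensitivity scenario.

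The cost is a few sentences. The number of patients, endpoint, significance level and analysis stay the same. The stated planning effect becomes smaller, and the reliance on a low acupuncture-arm SD becomes visible.

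### The completers' analysis is triggered only by significantly higher control dropout: a one-directional, low-power rule that adds it where it is most open to selection bias

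*Protocol article*

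**What the plan says.** All of the rules are in the protocol article, under Sample size calculation and statistical analysis.

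- Analysis principle: "the data analysis will be based on the intention-to-treat (ITT) principle regarding baseline characteristics".
- Conditional analysis: "If there are significantly more dropouts in the control group than in the treatment group, we will conduct a secondary analysis". The population is restricted, as a "secondary analysis of subjects who have completed the treatment according to the protocol". The test that decides whether the excess is significant is not named. For significance in general the section says "The significance levels will be two-sided and reported at a 5 % level".
- Missing data: "Missing data will be assumed to be missing randomly and will be imputed using multiple imputation". This is a general rule for all missing data.

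The Discussion, listing limitations, adds: "Due to the use of a sham acupuncture control, a relatively high rate of dropouts might be observed in the control group". It then says of blinding that "there is a risk that the blinding method may be unsuccessful in control participants, as the blunt tip needle will not leave puncture holes".

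**The concern.** The Discussion names a specific threat: patients may leave the sham arm more often, and some may realise that they are on sham. Dropout related to lack of benefit is then plausible. The stated reaction to an observed excess of control dropout is an extra analysis of those who stayed. Three features make this a poor robustness check.

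1. **Timing.** When dropout is related to outcome, the gap between completers and all randomised patients grows with the dropout rate. If the rate is much higher in one arm, the two selection effects no longer cancel. The rule adds the completers' analysis in exactly that case.
2. **Direction.** Excess dropout in the acupuncture arm triggers nothing.
3. **Gate.** A significance test on dropout counts with 34 per arm misses large imbalances, and since it is unnamed, the choice of test can decide whether the analysis exists.

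At stake is how a secondary result is read. If it agrees with the primary result, it may be taken as reassurance that it cannot give. If it disagrees, the reader cannot tell a real problem from selection.

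**Working it through.** **Inputs from the article.** 34 per group; 90 % power; two-sided 5 %; 20 % dropout, not split by arm; sham decrease 6.2 with SD 10.3; a figure of 13.3 with SD 4.5 for acupuncture; NIH-CPSI total score at baseline and weekly to week 8 (Table 1). Dropout rates by arm and the reason for leaving are assumptions.

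**Step 1: the plan's own figure.** Read 13.3 as the acupuncture decrease, so the difference is 13.3 − 6.2 = 7.1. Pooled SD = √((4.5² + 10.3²)/2) = 7.95. n = 2 × (1.960 + 1.282)² × 7.95² / 7.1² = 26.3, so 27 per group; 27/0.8 = 33.75, so 34. The planned size reproduces, and this point does not depend on a sample-size error.

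**Step 2: how often the trigger fires.** Sum the binomial probabilities over all pairs of dropout counts (34 per arm) in which control is higher and the two-sided p is below 0.05.

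| Acupuncture v control dropout (assumed) | Fisher | Chi-square |
|---|---|---|
| 20 % v 20 % | 1 % | 3 % |
| 15 % v 25 % | 11 % | 18 % |
| 10 % v 30 % | 44 % | 57 % |
| 5 % v 35 % | 86 % | 92 % |

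The last three rows average the planned 20 %. With 3 acupuncture dropouts, control needs 10 (chi-square, p = 0.031) or 11 (Fisher, p = 0.033). At 3 v 10, Fisher gives p = 0.062, so the unnamed test decides.

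**Step 3: bias in the completers' comparison.** Let z be lesser improvement in SD units, standard normal, and P(leave) = 1/(1 + exp(−a − ln 2 × z)), with a set to give the required dropout rate. The completers' mean improvement is then overstated by −E[z | stay] SDs.

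- 30 % dropout: 0.190 SD. Sham, SD 10.3: 0.190 × 10.3 = 1.96 points.
- 10 % dropout: 0.066 SD. Acupuncture: 0.066 × 4.5 = 0.30 points, or 0.066 × 10.3 = 0.68 points if its SD is as large as sham's.
- Net at 10 % v 30 %: 1.96 − 0.68 = 1.3 to 1.96 − 0.30 = 1.7 points. Against the planned 7.1 this is 18 % to 23 %.

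Sham completers look better than all sham patients, so the bias runs against acupuncture. If good responders leave instead, the sign reverses.

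**Step 4: completers compared with imputation.** A large-sample simulation used eight weekly scores, a true difference of 0, an SD of 5.25 for the eight-week mean in both arms, outcome-related dropout after week 3, and imputation by arm from the first three weeks. Absolute bias in points:

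| Dropout | Completers, dropout depends on observed scores | Completers, on unobserved scores | Imputation, on observed scores | Imputation, on unobserved scores |
|---|---|---|---|---|
| 20 % v 20 % | 0 | 0 | 0 | 0 |
| 10 % v 30 % | 0.9 | 1.0 | 0 | 0.4 |
| 5 % v 35 % | 1.4 | 1.6 | 0 | 0.7 |

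The completers' analysis fails under both mechanisms once dropout is unequal. Imputation fails only when dropout depends on scores that were not observed.

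**The case against.** The completers' analysis is secondary. It is added to the main analysis and replaces nothing, so the primary estimate is the same whether or not the trigger fires. That stands, and it limits the severity.

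A reader might infer that unequal dropout also undermines the multiple imputation. The article does not support this. Imputation is its general rule for missing data, not its answer to unequal dropout, and a difference in dropout rates between arms does not break the missing-at-random assumption. Scores are collected every week, so a patient who leaves for lack of benefit will often have recorded that first.

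A reader might also infer that the authors expect informative dropout. They say only that "a relatively high rate of dropouts might be observed in the control group", and they do not say that it would depend on unobserved scores.

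The bias figures can be pressed too hard. The 1.96 points belong to the sham arm alone; only the net figure bears on the comparison. The SD of 10.3 is for change after 10 weeks of sham in a cited trial, whereas the primary outcome averages eight weekly scores, which is one reason the simulation gives smaller values. In the scenario where poor responders leave sham, the bias is conservative.

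The absence of a sensitivity analysis for data not missing at random could be left to an analysis plan that is not shown, so it is not counted as a fault here. Finally, the phrase attaching ITT to baseline characteristics reads as awkward wording. Imputing missing data and calling the completers' analysis secondary make sense only if the main outcome comparison is ITT.

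What the objection does not remove is the trigger itself, which is a stated rule that a fuller document would have to correct.

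**Conclusion.** The concern holds for the dropout-triggered rule; it should be fixed, but it does not threaten the primary estimate. The rule ignores excess dropout in the acupuncture arm, fires only 44 % to 57 % of the time at 10 % v 30 % and 11 % to 18 % at 15 % v 25 %, and adds the completers' analysis where selection distorts it most. The net distortion at 10 % v 30 % is about 1.3 to 1.7 points against acupuncture under the assumed odds ratio of 2 per SD, or 0.9 to 1.0 in the simulation. These sizes rest on assumed dropout rates and mechanisms, and the direction depends on who leaves. The rule is therefore a poor check on the control dropout that the Discussion says might occur. The stronger conclusions, that the imputation is invalid or that the primary comparison is not ITT, are not supported.

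**What to change.** - Delete the dropout-triggered rule. Run the per-protocol analysis whatever the dropout in either arm, and label it supportive.
- Keep multiple imputation as primary, and state that the model includes arm and all observed weekly NIH-CPSI scores.
- Use a delta-adjusted imputation as the robustness check for differential dropout: worsen the imputed scores in steps, separately by arm, and report where the conclusion changes.
- Reword the ITT sentence to say that efficacy outcomes are analysed in all randomised patients as randomised.

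The cost is wording and one extra sensitivity analysis, with no new data. To be credible, the change should be made before unblinding.
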